## 5.4 Safety Objectives

The overall safety objective of this study is to evaluate a single 25 mg oral dose of psilocybin compared to an active placebo in incidence, severity and frequency of Adverse Events (AEs), Treatment Emergent AEs (TEAEs), Solicited AEs, and Serious Adverse Events (SAEs) before, during and after the dosing session and at all follow-up visits.

### 5.4.1 Specific Safety Monitoring Objectives

Safety will be continually evaluated by study staff through monitoring and assessment of AEs, vital signs, concomitant medication use, physical exams, on-site rater administered measures, and integration with session Facilitators. The study will also assess abuse liability, including non-clinical, illicit use of psilocybin and other psychedelics and other illicit and non-prescribed drug use via the AUDIT and DUDIT, participant self-report, and urine drug testing per the Schedule of Assessments.

### 5.4.2 Safety Endpoints

Specific safety endpoints are as follows:

Differences between the psilocybin and active placebo groups in:

- Incidence of AEs by severity
- Incidence of AEs leading to termination from the study
- Incidence of TEAEs
- Incidence of TEAEs by severity
- Incidence of solicited AEs
- Incidence of solicited AEs by severity
- Incidence of SAEs

## 5.5 Outcome Measures

### 5.5.1 Montgomery-Asberg Depression Rating Scale (MADRS)

The MADRS is a 10-item depression rating scale developed in 1979 to be more sensitive to symptom changes induced by antidepressants than were currently available instruments. The MADRS has been used for assessing primary outcomes in registration trials for new pharmacological agents for treating MDD, whether these agents are traditional monoamine modulators or agents with novel mechanisms of action (e.g., esketamine). The MADRS includes questions on the following symptoms 1) Reported sadness, 2) Apparent sadness, 3) Inner tension, 4) Reduced sleep, 5) Reduced appetite, 6) Concentration difficulties, 7) Lassitude, 8) Inability to feel, 9) Pessimistic thoughts, and 10) Suicidal thoughts. Items are scored via a clinical interview that progress from more broadly phrased questions about symptoms to more detailed queries that allow a precise rating of severity. Items are rated to capture the patient's clinical state over the prior week. Each item yields a score of 0 to 6, and higher scores indicate more severe depression. The overall score ranges from 0 to 60.

Various studies have suggested cut scores from  $< 9$  to  $< 12$  as a definition of remission. For the current study, remission will be defined as a score  $\leq 10$ . Response will be defined as  $\geq 50\%$  decrease compared to the last measurement before dosing.

MADRS-S is the self-rating version of MADRS. Apart from item 1 in MADRS, that is deleted from MADRS-S, the two scales are identical.

To reduce the risk of functional unblinding during collection of the primary study outcome measure, MADRS assessments will be conducted by a blinded rater. Raters will be blinded to participant allocation. At any occasion, if a face to face interview is not possible, a non-recorded video interview via an encrypted link will take place.

MADRS ratings will be performed at screening, PET1, day 0, 8, 15, 42, 180 and 365.

At day of dosing, results of MADRS (item 2-10) and MADRS-S before dosing will be used for validation purposes.

There is a lack of scientific evidence supporting that any instrument has sufficient accuracy to predict future suicide with 80% sensitivity and 50% specificity or better. However, MADRS item 10 (MADRS-S item 9) address suicidal ideation. A score of  $\geq 5$  at any time point suggests that a participant may be experiencing a level of active suicidal ideation and will necessitate clinical assessment, management and disposition.

The result on each MADRS item will be documented by the interviewer in the eCRF at time of interview.

#### **5.5.1.1 MADRS self-rating (MADRS-S)**

In order to get preliminary information on time to response and remission, duration of clinical effect, the self-rating version of MADRS will be administered at web-screening, PET1, day 0 prior to dosing, and day 1-8, 15 and monthly from day 42, 180 and 365 electronically via the participants smart phone or computer at the site as implemented the Region Stockholm web based patient interface 1177.se.

#### **5.5.2 Sheehan Disability Scale (SDS)**

The SDS will be utilized to determine the impact of psilocybin vs. placebo on functional disability (psychosocial functioning). This will be a key secondary endpoint for the current study. The SDS is a composite of three self-rated items designed to measure the extent to which three major sectors in the patient's life are impaired by psychiatric symptoms, including depression. This scale has been used widely in psychopharmacology randomized controlled trials and has been accepted by the Food and Drug Administration (FDA) for functional disability labeling. The SDS uses visual-spatial, numeric, and verbal descriptive anchors simultaneously to assess disability across three domains: work, social life, and family life. The SDS was developed as an intervention outcome measure that would be sensitive to change and to drug placebo differences over time. The SDS asks patients to rate the extent to which his or her 1) work/school, 2) social life or leisure activities, and 3) home life or family responsibilities are impaired by his or her symptoms on a 10-point visual analog scale. There are verbal descriptors for the points on the scale as well as numerical scores that provide more precise levels of the verbal descriptors. Typically, four scores are derived from the scale in research studies – one for each of the work, social life and family life disability measures and an aggregate total score of these three scores combined.

SDS is a self-report instrument that will be collected electronically at day -3, 0, 8, 15, 42 and then monthly until 365, via the participants smart phone or computer as implemented the Region Stockholm web-based patient interface 1177.se.

#### **5.5.3 General Anxiety Disorder 7 (GAD-7)**

GAD-7 was originally designed as a brief screening tool and symptom severity measure for GAD, but is increasingly being used as a broad general measure of anxiety, sufficiently sensitive to detect panic disorder, social phobia, and posttraumatic stress disorder. The self-

report questionnaire, designed to assess the patient's status during the previous 2 weeks, is widely used in both research and clinical settings. It contains seven items with a score range from 0 to 21, and has both high levels of internal consistency (a 1/4 .89 – .92) and test – retest reliability (r 1/4 .83).

GAD-7 is a self-report instrument that will be collected electronically at day -3, 0, 8, 15, 42 and then monthly until 365, via the participants smart phone or computer at the site as implemented the Region Stockholm web-based patient interface 1177.se.

#### **5.5.4 Clinical Global Impression – Improvement and Severity (CGI-I and CGI-S)**

The CGI rating scales are measures of symptom severity, intervention response and the efficacy of interventions in intervention studies of patients with mental disorders. The CGI-S is a 7-point scale that requires the rater to rate the severity of the patient's illness at the time of assessment, relative to the clinician's past experience with patients who have the same diagnosis. Possible ratings are:

1. Normal, not at all ill
2. Borderline mentally ill
3. Mildly ill
4. Moderately ill
5. Markedly ill
6. Severely ill
7. Among the most extremely ill patients

CGI-I is a 7-point scale that requires the rater to rate the change of the patient's illness compared to the baseline (ie first) assessment regardless of cause. Possible ratings are:

0. Not assessed
1. Very much improved
2. Much improved
3. Minimally improved
4. No change
5. Minimally worsened
6. Much worsened
7. Very much worsened

CGI- S and CGI-I will be collected at the same time points (day 0 (only CGI-S), 8, 15, 42, 365), by the same rater, as MADRS, and the results will be documented by the interviewer in the eCRF at time of interview.

#### **5.5.5 EQ-5D**

EQ-5D is a valid, reliable and responsive self-rating of quality of life. Five dimensions of quality of life, mobility, self-care, usual activities, pain/discomfort and anxiety/depression are quantified in three (EQ-5D-3L) or five (EQ-5D-5L) levels of severity. There is also a visual analogue scale (VAS) for quantification of overall health status.

EQ-5D is a self-report instrument that will be collected electronically at day -3, 0, 8, 15, 42 and then monthly until 365, via the participants smart phone or computer as implemented the Region Stockholm web-based patient interface 1177.se.

### 5.5.6 Challenging Experience Questionnaire (CEQ)

CEQ is a validated 26-item self-report scale developed in 2016 to measure acute adverse psychological reactions to psilocybin and other classic hallucinogens. At the end of the dosing session, participants rate the degree to which at any time during that session they experienced potential adverse symptom on a scale from 0 (none; not at all) to 5 (extreme; more than ever before in my life).

CEQ will be administered by the Facilitators on paper and then transferred to the eCRF by study personnel, upon completion of the dosing session when all behavioral effects of the intervention have resolved.

### 5.5.7 Mystical Experience Questionnaire (MEQ-30)

The MEQ is a self-report measure developed to assess the immediate effects of classic psychedelics. It is based on Stace's conceptual framework of mystical experiences, and covers the major dimensions of classic mystical experience: unity, transcendence, noetic quality, sacredness, positive mood, and ineffability/paradoxicality. The MEQ has been administered in various forms in a number of studies over the past 50 or more years. Items on the questionnaire are rated on a 6-point scale, from 0 (none; not at all) to 5 (extreme; more than ever before in my life). A factor analysis conducted by MacLean et al. found that the most recent version (MEQ30), is a psychometrically sound instrument for assessing psychedelic-occasioned mystical experiences.

MEQ-30 will be administered by the Facilitators on paper and then transferred to the eCRF by study personnel, upon completion of the dosing session when all behavioral effects of the intervention have resolved.

### 5.5.8 Emotional Breakthrough Inventory (EBI)

The EBI is a new 6-item scale developed by researchers at Imperial College in London, that assesses the presence and severity of emotionally challenging/distressing experiences that can occur during a psychedelic experience. The scale utilizes visual analog responses captured on a line from “not at all” to “very much so”. Experiences queried include 1) facing emotionally difficult feelings that are usually pushed aside; 2) experiencing a resolution of a personal conflict/trauma; 3) being able to explore challenging emotions and memories; 4) having an emotional breakthrough; 5) getting a sense of closure on an emotional problem, and 6) achieving an emotional release followed by a sense of relief.

EBI will be administered by the Facilitators on paper and then transferred to the eCRF by study personnel, upon completion of the dosing session when all behavioral effects of the intervention have resolved.

### 5.5.9 Treatment Expectation

Treatment Expectation is a compilation of questions regarding the participants' expectation of the forthcoming treatment in five areas: Their treatment expectation; whether they will feel safe and seen during sessions; if they think the treatment will help them; and if the treatment will make them satisfied. The questions are answered on a scale ranging from 0 (not at all) to 4 (to a very high degree). At the end of the form, participants will also answer a question regarding how much they think the treatment will reduce their depression on a scale ranging from 0 to 100.

The questionnaire will be administered on paper and then transferred to the eCRF by a study coordinator, before the first treatment session.

### 5.5.10 Treatment Evaluation

Treatment Evaluation is a compilation of questions regarding the participants' treatment experience in five areas: Their experience during sessions; if they felt safe and seen; if they think the treatment was helpful; and if the treatment made them satisfied. The questions are answered by the participants on a scale ranging from 0 (not at all) to 4 (to a very high degree). At the end of the form, participants will also answer a specific question regarding how much they think the treatment will reduce their depression, on a scale ranging from 0 to 100, and a question regarding any recent lifestyle changes.

The questionnaire will be administered on paper and then transferred to the eCRF by a study coordinator, after the last treatment session.

### 5.5.11 Acceptance in Action Questionnaire (AAQ-II)

AAQ-II is a brief 7-item measure of psychological flexibility with a satisfactory structure, reliability and construct validity. Participants score value statements on a scale ranging from 1 (never true) to 7 (always true) to capture six core processes of psychological flexibility: Present moment awareness; Acceptance of experiences; Defusion from the literal belief in thoughts; Values clarification; The identification of specific behaviors in the service of those values (committed action); and, Contact with a flexible experience of the self (self-as-context). Lower scores on the AAQ-II indicate greater levels of psychological flexibility and predict a range of outcomes including wellbeing in patients with anxiety and depression. The theory of psychological flexibility has proposed to fit with the phenomenological experience of psychedelics, and thus act as a good research guide for how these treatments work in the acute phase, and may lead to lasting change.

AAQ-II will be administered together with ALIVE by the Facilitators on paper and then transferred to the eCRF by study personnel, in conjunction with the first (Preparation session), fourth (Integration session number two), and fifth (Integration session number three) treatment session. At Day 42 and 365, AAQ-II will be administered on paper and then transferred to the eCRF by a study coordinator.

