## 5.3 Exploratory Objectives and endpoints

The exploratory objectives of this study are to evaluate the efficacy of a single 25 mg dose of psilocybin for MDD compared to an active placebo in medically-healthy participants ages 20 to 65, measured as between-group differences in:

- Change in p11 concentration in PBMC subsets from Baseline to day 15 Post dose
- Change in BDNF and VEGF concentration in plasma from Baseline to day 15 Post dose
- Change in kynurenic acid in CSF from Baseline to day 15 Post dose
- Change in monoamine and monoamine metabolites in CSF from Baseline to day 15 Post dose
- Change in cytokine concentration (exact markers to be determined based on current literature at time of analysis) in CSF from Baseline to day 15 Post dose
- Change in metrics of whole-brain connectomics and hub characteristics of medial and ventrolateral prefrontal cortex as well as orbitofrontal cortex in the psilocybin treated group as compared to the placebo group, and in relation to clinical outcome (MADRS) as well as PET-outcome (resting state fMRI).
- Change in influence of top-down priors in an instructed fear learning paradigm and its relation to a change in activity of the ventromedial prefrontal cortex and lateral orbitofrontal cortex in the psilocybin treated group as compared to the placebo group, and in relation to clinical outcome (MADRS) as well as PET-outcome (tasked based fMRI).
- Change in Emotion detection under perceptual uncertainty and perspective-shifting ability in relation to large-scale network activity patterns in the psilocybin treated group as compared to the placebo group, and in relation to clinical outcome (MADRS) as well as PET-outcome.
- Change in anxiety symptoms from Baseline to post-dose Day 8, 15, 42 and 365
- Change in functional disability to post-dose Day 8, 15, 42 and 365
- Change in health-related meaning of life and satisfaction with life from Baseline to post-dose Day 8, 15, 42 and 365
- Change in psychological flexibility from Baseline to post-dose Day 8, 15, 42 and 365
- Correlations between biomarkers and scales

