### 5.5.12 Actively Living and Interconnecting Vitality in one's Embedded-world (ALIVE)

Alive (Bond and Dowling, *in press*) is another measure of psychological flexibility that measures three indivisible, or interwoven, activities: Learning to actively tune-in to perceptions; Discover multiple possibilities; Take a stand as the person (the participant) wish to become. ALIVE is a brief 6-item self-report scale with value statements on a scale ranging from 1 (never true) to 7 (always true). Psychometric analyses with over 13.000 participants across eight studies appear to support the construct validity of the ALIVE measure. Analyses include exploratory and confirmatory factor analyses, (supportive) CFA invariance analyses, structural equation models that examine concurrent validity, autoregressive longitudinal panel studies, and quasi-experiments (Bond and Dowling, *in press*).

ALIVE will be administered together with AAQ-II by the Facilitators on paper, and then transferred to the eCRF by study personnel, in conjunction with the first (Preparation session), fourth (Integration session number two), and fifth (Integration session number three) treatment session. At Day 42 and 365, ALIVE will be administered on paper and then transferred to the eCRF by a study coordinator.

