### 5.5.13 Meaning of Life Questionnaire (MLQ)

MLQ is a brief 10-item self-report measure of the search for and presence of meaning in life, with value statements on a scale ranging from 1 (absolutely untrue) to 7 (absolutely true). MLQ has shown to be a reliable, structurally sound measure of the search for/presence of meaning, and presents a number of improvements over other measures of meaning of life, including more precise measurement, greater structural stability, and assessment of the search for meaning.

MLQ will be administered together with SWLS by the Facilitators on paper, and then transferred to the eCRF by study personnel, in conjunction with the first (Preparation session), fourth (Integration session number two), and fifth (Integration session number three) treatment session. At Day 42 and 365, MLQ will be administered on paper and then transferred to the eCRF by a study coordinator.

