### 5.5.14 Satisfaction with Life Scale (SWLS)

SWLS was developed as a measure of the judgmental component of subjective well-being. The high convergence of self- and peer-reported measures of subjective well-being and life satisfaction provide strong evidence that subjective well-being is a relatively global and stable phenomenon. SWLS is shown to be a valid and reliable measure of life satisfaction, suited for use with a wide range of age groups and applications. SWLS is a brief 5-item self-report measure with value statements on a scale ranging from 1 (strongly disagree) to 7 (strongly agree).

SWLS will be administered together with MLQ by the Facilitators on paper, and then transferred to the eCRF by study personnel, in conjunction with the first (Preparation session), fourth (Integration session number two), and fifth (Integration session number three) treatment session. At Day 42 and 365, SWLS will be administered on paper and then transferred to the eCRF by a study coordinator.

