### 5.5.15 Working Alliance Inventory-Short (WAI-S)

The Working Alliance Inventory and the Working Alliance Inventory-Short are widely used measures of alliance in both psychotherapy and research settings. The WAI was originally derived from a well-researched framework on the working alliance developed by Bordin. WAI-S contains 12 items rated on a seven points scale. It provides a summary of the total working alliance and three subscales to assess primary components of the working alliance: Goal (i.e., agreement with regard to the treatment goals), Task (i.e., agreement with regard to the tasks) and Bond (i.e., the empathic bond between the client and the therapist). In this study, the Facilitator and the participant each complete WAI-S at the end of the same treatment sessions. Both forms also contain two additional questions regarding empathy and partnership/collaboration, as defined in the MITI.

The participants' form will be administered on paper and then transferred to the eCRF by a study coordinator, after session one (Preparation session) and four (Integration session number two). The Facilitators' form will be answered by the Facilitators on paper, and then transferred to the eCRF, after the same treatment sessions.

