### **9.10 Blinding Related to Delivery of Study Interventions and Collection of Outcome Data**

In order to secure blinding for remaining patients in the study, no patient will receive information of the actual treatment received, with the exception of a serious adverse event, and then at the discretion of the PI or designee.

As with any interventions that produce noticeable psychological effects following administration, blinding psilocybin poses unique challenges.

Prior to start-up, all study site staff will receive extensive training in basic research principles of maintaining the study blind and ensuring only appropriate personnel have access to this information.

Session Facilitators, who will be in the room with participants throughout their dosing sessions, may become functionally unblinded as a result of participants demonstrating changes in behavior and/or speech suggestive of a psychedelic experience, or as a result of participants not demonstrating these types of changes. They will receive written information not to share their thoughts on the outcome of randomization with anyone.

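### Five exploratory self-report scales are handed out at Days 8 and 15 by Facilitators who may be functionally unblinded, an avoidable risk of arm-dependent reporting bias

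*Protocol*

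**What the plan says.** **Who gives out the forms.** Five participant self-ratings share one route.

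- AAQ-II (5.5.11): "AAQ-II will be administered together with ALIVE by the Facilitators on paper and then transferred to the eCRF by study personnel".
- ALIVE (5.5.12): "ALIVE will be administered together with AAQ-II by the Facilitators on paper, and then transferred to the eCRF by study personnel".
- MLQ (5.5.13): "MLQ will be administered together with SWLS by the Facilitators on paper, and then transferred to the eCRF by study personnel".
- SWLS (5.5.14): "SWLS will be administered together with MLQ by the Facilitators on paper, and then transferred to the eCRF by study personnel".
- LEQ (5.5.16): also given on paper by the Facilitators.

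The first four are tied to the preparation session and to integration sessions 2 and 3. In 5.5.16 LEQ is tied to integration sessions 2 and 3 only. Table 1 enters the two Facilitators (F1;F2) against these scales at Days 8 and 15. At Days 42 and 365 the same sections no longer name the Facilitators. They mention a study coordinator, and Table 1 lists MD1, a code whose legend includes the study coordinator.

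**Blinding of the Facilitators.** Under 9.1 the same two Facilitators stay with the participant through preparation, dosing and integration. Section 9.10 says they "may become functionally unblinded as a result of participants demonstrating changes in behavior" or speech, or through the absence of such changes. The safeguard stated for them is written information telling them not to share their thoughts on allocation.

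**Use of the data.** Section 5.3 lists among the exploratory between-group differences "Change in psychological flexibility from Baseline to post-dose Day 8, 15, 42 and 365", with a parallel entry for meaning of life and satisfaction with life. LEQ appears among the exploratory outcome measures in the synopsis but has no entry of its own in 5.3.

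**The concern.** The person who gives out a self-report form can influence the answers even without scoring them. Here the forms ask about flexibility, meaning, satisfaction and lasting effects of the dosing day, and they come from the two people who guided that day. If a participant feels some pull to report benefit to them, and if both sides have a view on which capsule was taken, the pull may differ between arms. Part of a Day 8 or Day 15 group difference could then be reporting rather than effect, and no later analysis could separate the two.

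There is a second, smaller issue. Because the administrator changes between Day 15 and Day 42, an early difference that fades could reflect a waning effect or the Facilitators no longer being involved. Section 5.5.11 presents psychological flexibility as a guide to how these treatments work, so the early contrasts are likely to be read as evidence on mechanism.

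**Working it through.** **1. Self-ratings at Days 8 and 15, side by side**

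| Measure | Route | Source |
|---|---|---|
| MADRS-S, GAD-7, EQ-5D, SDS | Electronic, 1177.se | 5.5.1.1, 5.5.2, 5.5.3, 5.5.5 |
| Participant WAI-S (Day 8) | Paper, coordinator | 5.5.15 |
| Treatment Evaluation (after last session) | Paper, coordinator | 5.5.10 |
| AAQ-II, ALIVE, MLQ, SWLS, LEQ | Paper, Facilitators | 5.5.11 to 5.5.14, 5.5.16 |

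The rater-scored MADRS has a blinded rater (5.5.1). The five scales are thus the exception, and routes that avoid the Facilitators already exist at the same visits. A nurse (MHS_N) is listed in Table 1 on Day -1 and Day 8 for a WAI-S form and on Day 15 for Treatment Evaluation.

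**2. Which time points are exposed**

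The preparation session falls before randomization (9.2, 10.4.1), so the Day -1 answers cannot depend on arm. Days 42 and 365 are not assigned to the Facilitators. Only Days 8 and 15 remain.

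**3. Size**

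No figure in the documents measures this bias, so there is nothing to reproduce for it. The method below can be checked against the one related figure, the sample size in 16.1 (15 per group, difference 11, SD 10, two-sided 5%), which concerns the primary endpoint only.

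- Noncentrality: λ = δ × √(n/2), where δ is the difference in SD units. Degrees of freedom: 2n − 2.
- Rejection probability: 1 − F(t_c; df, λ) + F(−t_c; df, λ), where F is the noncentral t distribution and t_c the two-sided 5% critical value.
- For the plan's case δ = 11/10 = 1.1, n = 15, df = 28 and λ = 1.1 × √7.5 = 3.01. Power is 82.8%, which agrees with the stated 80%. With n = 14 it is 79.99%.

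Now set the true effect to zero and let δ be an assumed arm-dependent reporting shift, in SDs of the analysed change score, again with 15 per arm:

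| Assumed shift (SD) | λ | False-positive rate | Excess over 5% |
|---|---|---|---|
| 0 | 0 | 5.0% | 0 |
| 0.1 | 0.27 | 5.8% | 0.8 points |
| 0.2 | 0.55 | 8.3% | 3.3 points |
| 0.3 | 0.82 | 12.5% | 7.5 points |
| 0.5 | 1.37 | 26.2% | 21.2 points |

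These rates would apply to any bias of that size in any endpoint with 15 per arm. They do not show that a shift of this size is present.

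**4. The WAI-S rows of Table 1**

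Section 5.5.15 has the participant's form "administered on paper and then transferred to the eCRF by a study coordinator, after session one (Preparation session) and four", and has the Facilitators answer their own form. Table 1 has a row WAI-S, tagged SRF and assigned to the nurse, and a row WAI-S T, tagged SRP and assigned to F1;F2. The legend defines SRP as the patient's rating and SRF as the facilitator's. If T stands for therapist, which the legend does not say, the staff assignments agree with 5.5.15 in keeping the participant's form away from the Facilitators, and only the two tags are interchanged.

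**The case against.** **Functional unblinding is only a possibility.** A reader might infer that the protocol expects the Facilitators to be unblinded. Section 9.10 does not say so, and it adds the instruction not to share their thoughts. This stands. The instruction, however, does not address a participant's wish to please the people handing over the form.

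**Bias is not shown.** A reader might infer that the Day 8 and Day 15 contrasts are biased. The documents do not support that. These are fixed-response self-ratings, the Facilitators do not score them, and study personnel transfer the answers. Tying a form to a session does not establish that it is filled in after the session or within the Facilitators' sight. This stands, and the point is limited to risk. The same silence means that nothing in the text prevents the Facilitators from seeing the answers.

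**Participants may guess their own arm.** That affects every self-report, including those on 1177.se, so rerouting removes only the Facilitator-related part. This stands.

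**The change at Day 42 is the same in both arms.** Each visit's between-group contrast still compares like with like. This stands; only comparisons across visits are complicated.

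**Table 1 and WAI-S.** A reader might infer that Table 1 undoes the safeguard in 5.5.15. The staff assignments do not support that if T marks the therapist's form. What remains is a labelling slip.

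**Little depends on these scales.** They are exploratory, their results stay out of the Clinical Study Report (synopsis, Exploratory Objectives), and 16.4.2 promises cautious interpretation. This stands and sets the severity, although the results are still meant for journals.

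**Conclusion.** The point holds as a minor, avoidable design weakness. At Days 8 and 15, AAQ-II, ALIVE, MLQ, SWLS and LEQ are given out by staff whom the protocol acknowledges may be functionally unblinded, while comparable self-ratings at the same visits are collected without them. The resulting exploratory contrasts are at risk of arm-dependent reporting bias. Its direction and size are unknown, and the tabulated rates are illustrations that rest on an assumed shift, 15 evaluable participants per arm and a simple t-test. The primary endpoint and all secondary endpoints are unaffected, because none uses these scales. The WAI-S tags are a separate clerical matter, on the reading that T means therapist.

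**What to change.** In 5.5.11 to 5.5.14, 5.5.16 and Table 1:

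- Have participants complete these forms before the Facilitator session begins, and still after the MADRS interview, as 5.6.2 requires.
- Collect them through 1177.se where feasible. Otherwise the nurse already listed on Days -1, 8 and 15 gives them out on paper and takes them back in a sealed envelope.
- State that the Facilitators do not see the answers.
- Keep non-Facilitator administration at Days 42 and 365, by the same route if 1177.se is used.

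Separately, interchange the SRP and SRF tags on the two WAI-S rows of Table 1 to match 5.5.15, and define T in the legend.

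**Cost.** Wording in five subsections and one table, with no added visit or staff. The burden is handling envelopes or adding short forms to 1177.se. The documents do not show whether that system can take all five forms, hence the paper alternative. The nurse is not listed at Days 42 and 365, so on paper the existing staff there should continue. The change will not remove bias from participants guessing their own arm, and reports of these scales should say so.
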